## Discussion

3

AI with deep learning needs good training data to work properly. Thus, we put a premium on the quality of training image data in the development of our AI. Experienced and qualified readers will interpret mammograms and define the outline of the malignant or benign lesions. To delineate the outline precisely, surgical pathology reports or the results of other imaging modalities will be taken into account whenever possible. The diagnosis will be confirmed by histopathology. Benign diseases without available pathological results will be clinically diagnosed after at least 2 years of follow-up. To avoid biased collection toward a particular lesion, a target number of images has been set according to each radiographic finding in breast cancer or in each benign disease.

Mammographic images will be obtained from multiple participating centers. The DM images will be acquired with devices from various vendors. The images used in this study will be taken from women aged 20 or older (not confined to the recommended screening age), and originating not only from screening but also from clinical practice. Larger and more advanced breast cancers are expected from clinical practice, with different characteristics from screen-detected cancers. These various kinds of data will increase the generalizability of our AI algorithms. Alongside images, we will collect clinicopathological features of each case, including pathological diagnosis, tumor diameter, hormone receptor status, HER2 status, breast density, and vendors. This will enable us to perform detailed analysis of which patient population is more suitable for AI reading.

Our study has a limitation. The dataset will come only from Japanese women. Thus, our AI system might not be applicable to Caucasian patients. However, it will probably work well in Asian women who have similar breast density, size, and shape to Japanese women.

Japan has a double reading system in screening mammography. When the ability of AI reading is shown to be on a par with that of human reading, images of normal breasts or benign lesions that do not have to be read by a human can be selected by AI beforehand (the first reader role). This AI preselection might obviate the need for double reading. However, future studies will be required to clarify how much the workload of readers is reduced or which threshold of cancer probability for alerting humans is optimal.

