### Endpoints

2.3

The primary endpoint is the sensitivity and specificity of the AI system to detect breast cancer with the test image set. Sensitivity is calculated as the number of images in which the AI system correctly diagnoses cancer among all images with biopsy-proven cancer. Specificity is calculated as the number of images in which the AI system correctly diagnoses normal or benign lesions among all images without cancer.

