### Construction of an AI algorithm

2.5

The machine learning community has been applying deep learning in various medical imaging fields, including mammography images. Based on this work, we have developed a convolutional neural network. The neural network includes pairs of the convolutional layer and the pooling layer with the fully convolutional layers. The classification output is calculated by the softmax function.

From mammography images, corresponding masking images of breast lesions will be created manually, indicating the area of the lesions. Mammography images will then be cropped with rectangular patches so that the lesions are included in these patches, and patches will be classified as benign or malignant. Patches in which neither benign nor malignant tumors are included will also be cropped from the mammography images.

These patches will be randomly divided into the training dataset, the validation dataset, or the test dataset. The neural network will be fine-tuned to classify whether these patches contain either a benign or a malignant tumor, or neither of them.

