### Statistical analysis

2.6

The Breast Cancer Surveillance Consortium reported readers’ interpretive performance with sensitivity and specificity of around 85% and 90% respectively.^[24]^ The sensitivity of mammography was 77% in the J-SATRT trial conducted in Japan.^[25]^ Thus, we set the target sensitivity and specificity at 80% or more with the AI system. By referring to the design of previous studies.^[26]^ 15,000 DM images will be collected in this study. They will consist of 5000 images with breast cancer and 10,000 images with benign lesions. At least 1000 images of normal breasts will also be collected for use as reference data.

We will categorize images with breast cancer according to the main findings (mass, focal asymmetric density, calcification, architectural distortion). At least 750 images will be collected in each category.

There will be a limit on the number of accumulated images with each benign lesion. Simple cyst 1500; fibroadenoma or benign phyllodes tumor 1500; intraductal (intracystic) papilloma 1500; adenoma 100; adenomyoepithelioma 100; sclerosing adenosis 1000; mastopathy 1000; breast calcifications 4000; other benign disease 300 images.

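### The expected gain in generalisability is not tested: a random split of pooled data leaves practically every institution and vendor in both the training and the test set

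*Protocol article*

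**What the plan says.** The Discussion (section 3) describes the source of the data: "Mammographic images will be obtained from multiple participating centers", and "The DM images will be acquired with devices from various vendors". It adds that the women are not confined to screening age and that images come from clinical practice as well as screening. From all of this it concludes: "These various kinds of data will increase the generalizability of our AI algorithms".

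Section 2.5 (Construction of an AI algorithm) fixes how the test data arise. Patches are cropped from the mammograms, and "These patches will be randomly divided into the training dataset, the validation dataset, or the test dataset". No institution, vendor or outside dataset is set aside.

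Section 2.3 (Endpoints) ties the main result to that test set: "The primary endpoint is the sensitivity and specificity of the AI system to detect breast cancer with the test image set". Section 2.6 sets a target of at least 80% for both measures.

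The Discussion names one limitation: "Our study has a limitation. The dataset will come only from Japanese women". Vendor is among the case features to be collected ("including pathological diagnosis, tumor diameter, hormone receptor status, HER2 status, breast density, and vendors"), with a view to analysing which patients suit AI reading. It is not used as a unit for dividing the data.

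**The concern.** Variety in the training data and evidence of performance at a new place are different things. Variety is a sensible reason to expect broader applicability. Evidence needs test cases from a source the network has not met. A random division of one pooled collection supplies no such cases by design: the test patches share institutions, devices, image processing and local case selection with the training patches. Dividing by woman instead of by patch would not change this, so the point is separate from any leakage between patches of the same woman.

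At stake is the reading of the primary endpoint. The Discussion looks ahead to AI preselection of images that a human need not read, and possibly to dispensing with double reading. Such use would extend beyond the contributing centres. The future studies it calls for concern workload and the alert threshold, not performance at new sites.

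There is a second, conditional issue. If the proportions of cancer, benign and normal images differ by institution or vendor, a network can pick up source features as a cue to class, and a random split would reward that cue rather than expose it. The article does not state the class mix by source.

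**Working it through.** The article gives no split ratio, number of centres or figures by site, so there is no stated result to reproduce. What can be checked is whether a random split really puts practically every source on both sides.

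**Inputs**
- Method of division: random, with patches as the unit (section 2.5).
- Collection size: "15,000 DM images will be collected in this study", made up of 5000 cancer and 10,000 benign, plus at least 1000 normal (section 2.6).
- Assumed, not in the article: test share f, and number m of patches from a given institution or vendor.

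**Formula.** If each patch is assigned independently, the probability that a source with m patches is absent from the test set is (1 − f)^m.

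| m | f = 0.1 | f = 0.2 |
|---|---|---|
| 10 | 0.9^10 = 35% | 0.8^10 = 11% |
| 50 | 0.9^50 = 0.5% | 0.8^50 = 0.0014% |
| 100 | 0.9^100 = 0.003% | below 0.000001% |

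**Presence in both sets.** Suppose the validation share equals the test share, so that training takes 1 − 2f. At f = 0.1 and m = 50, the probability of appearing in both training and test is 1 − 0.9^50 − 0.2^50 + 0.1^50 = 0.995.

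**Whole collection.** If 15,000 images, one patch each, came equally from 50 centres, each would give 15,000 / 50 = 300 patches. The expected number of centres missing from a 10% test set is 50 × 0.9^300, about 10^−12.

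Only a contributor of a handful of patches could be absent, and then by chance. Under a split by woman the same formula applies with m as the number of women from that source.

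**Relevance of a source cue to specificity.** Section 2.3 counts all images without cancer in the denominator. At the stated minimum of normals, that is 10,000 + 1000 = 11,000 images, of which normals are 1000 / 11,000 = 9%. Any effect of a cue on specificity therefore depends mainly on how the benign images are spread over sources, which the article does not give.

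**The case against.** The strongest reply is that the study delivers what it promises. Section 2.1 aims to build a system and evaluate it, and section 2.3 confines the primary endpoint to the test set. Internal testing is a recognised stage of development. The quoted sentence is a forward-looking, comparative rationale in a protocol without results. It rests on age range and screening or clinical origin as well as on centres and vendors. The statement about other Asian women is hedged and rests on breast density, size and shape. All of this stands, and it means the planned internal estimate is not wrong. It does not supply a test of the expectation, nor explain why the only limitation named is the restriction to Japanese women. Results by vendor, which the recorded data allow, would cover only vendors seen in training.

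A reader might go further and infer that a vendor cue inflates both sensitivity and specificity. The article does not support this. Section 2.6 sets numbers by lesion type and states no allocation by site, and no class mix by source is given. Suppose 80% of cancers and 20% of normals came from vendor A, and images were called cancer on vendor alone. Sensitivity would be 80%, but specificity would be 1 − (8000 + 200)/11,000 = 25% if 80% of benign images also came from vendor A, and 1 − (5000 + 200)/11,000 = 53% if half did. The direction for specificity is open. Section 2.5 also does not restrict lesion-free patches to normal breasts. Those cropped from images that contain a lesion share their source with the lesion patches and carry no vendor cue.

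A reader might also infer a drop of a given number of points at a new site, enough to fall below the 80% target. The article contains nothing from which such a figure could be derived.

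Finally, leaving out institutions may give unstable estimates if centres are few, small or dominated by one. That is fair and shapes the fix.

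**Conclusion.** The point holds in a limited form. Under the stated random division, practically every institution and vendor will be in both training and test data: at an assumed 10% test share, the chance of absence is about 0.5% for a source with 50 patches and about 0.003% with 100. The primary sensitivity and specificity therefore describe sources already seen. The expected gain in generalisability is not tested, and this is not listed as a limitation.

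The conclusion rests on the division being as section 2.5 states it and on centres contributing more than a few patches each. The internal estimate itself is not shown to be biased by this. A source cue is possible if class mix varies by institution or vendor, but its size, and its direction for specificity, cannot be determined from the article. Nor can the difference in performance at a new institution. This is a worthwhile and fairly cheap improvement, not a fatal flaw.

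**What to change.** Keep the planned random-split estimate as the internal result. Add a secondary analysis on the images already collected:

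- Leave out each institution, or each vendor group, in turn; retrain on the rest and test on the part left out. Combine small centres into groups fixed in advance so that the estimates are stable.
- Report pooled sensitivity and specificity from these runs, with the spread across groups, beside the internal figures.
- Tabulate cancer, benign and normal images by institution and by vendor, so that a possible source cue can be judged.
- Base the generalisability statement on these results. If the analysis is not done, word the statement as an untested expectation and name the lack of testing at unseen institutions and vendors as a limitation.

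No new images are needed, and vendor is already among the features to be recorded; institution has to be kept as a grouping variable. The costs are the repeated training runs and an added analysis paragraph. Estimates will be sparse for small centres and for rare lesion types such as adenoma and adenomyoepithelioma, each capped at 100 images in section 2.6. The figures may also be less favourable than those from the random split.
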